## Abstract

**Background:**

The pattern of substance use in Iran is characterized by a high prevalence of opioid use and opioid use disorder (OUD). Although opioid maintenance therapy (OMT) has been introduced in Iran, approximately 50% of people with opioid use disorder remain unreached. Moreover, psychosocial treatment of OUD and common mental health symptoms during OMT is limited. Digital interventions have been shown to improve psychological distress, depression, anxiety, and post-traumatic stress disorder symptoms. In addition, providing psychoeducation and risk reduction counseling to prevent communicable diseases like HIV and infectious hepatitis is common via the Internet. However, despite these promising advances, no smartphone intervention in OMT has been investigated for the treatment of OUD and common comorbid mental health symptoms.

**Objective:**

We examine the effectiveness of adding a blended smartphone intervention based on community reinforcement approach, motivational interviewing- and cognitive behavioral therapy compared to OMT as usual that aims to improve OMT outcomes and addresses common mental health symptoms in OMT patients in Iran.

**Method:**

Adults with opioid dependence entering 8 treatment centers in Tehran, Iran will be randomly assigned to receive either OMT plus a smartphone intervention or OMT as usual. The primary outcomes will be the percentage of negative urine tests for illicit, non-prescribed use of opioids (opium, heroin, tramadol) and treatment retention. Secondary outcomes will include the longest period of abstinence from the illicit, non-prescribed use of opioids (opium, heroin, and tramadol) confirmed by urine samples, changes in communicable disease risk-taking behaviors, changes in stress and common mental health symptoms, and client satisfaction. Data analysis will follow the intention-to-treat principle and employ (generalized) linear mixed models.

**Discussion:**

This study will provide substantial knowledge for designing effective blended interventions for OUD. Moreover, it will investigate if treatment retention and OMT-related outcomes and common mental health symptoms can be improved by adding a smartphone intervention to OMT.

**Trial Registration:**

https://en.irct.ir/trial/53578.

**Supplementary Information:**

The online version contains supplementary material available at 10.1186/s12888-023-05007-0.

## Introduction

Iran has a high prevalence rate of opioid use. The 12-month prevalence of opioid use in the population aged between 15 and 64 is reported to be over 3.0%, and the 12-month prevalence of DSM-5 diagnosis of opioid use disorder (OUD) is 2.23% [1]. The gender gap in regard to opioid use in Iran is much larger compared to other countries [2, 3], which is likely due to socio-cultural factors [4, 5].

Over the past decades, consumption patterns have evolved from opium smoking – that still has a historical tradition – to heroin smoking and heroin injection, which has considerably increased the health consequences of opioid use in Iran [6, 7]. In fact, using non-sterile syringes is the most prevalent route (57.3%) of HIV transmission among all registered HIV-positive cases until the end of 2021 [8]. Furthermore, high prevalence rates for hepatitis C [7] and tuberculosis [9–11] have been reported among people who inject drugs in Iran.

Opioid maintenance therapy (OMT), using methadone and buprenorphine, was therefore introduced to respond to the HIV epidemic among those using opioids and scaled up rapidly [12, 13]. OMT programs are provided through a network of certified drug treatment centers and have shown promising effects for the treatment of OUD and for reducing the risk of HIV transmission [14–16]. However, there are limited resources to provide continuous psychosocial interventions necessary for the treatment of OUD and the management of common mental health symptoms, such as depression and anxiety, which are highly prevalent in patients with OUD [1].

Smartphone interventions for patients with OUD could help to close this gap by delivering psychological interventions with high fidelity while requiring fewer human resources and empowering individuals to self-manage mental health issues. The perceived anonymity, timeliness of access, and flexibility offered by digital interventions also evade commonly identified barriers to accessing care. Blended interventions that integrate face-to-face and digital interventions for patients with OUD could help to reduce this treatment gap. This study aims to develop a smartphone intervention and to deliver it in a blended treatment format for patients with OUD who enter OMT program and assess its effectiveness through a randomized controlled trial.

## Methods

### Study design

We will conduct a multi-center, two-arm, parallel-group randomized controlled trial (RCT) comparing an integrated community reinforcement approach- (CRA), motivational interviewing- (MI), and cognitive, behavioral treatment (CBT)-based smartphone intervention (called PROMPT for Promoting Recovery in Opioid Maintenance and Psychosocial Treatments) suitable for blended treatment in OMT with OMT as usual. Consequently, participants in the PROMT condition will receive access to the smartphone intervention in addition to OMT as usual; participants in the OMT as usual condition will receive OMT as usual but not access to PROMPT. The Ethics Committee of Tehran University of Medical Sciences (Code: IR.TUMS.MEDICINE.REC.1399.714) and the Ethics Committee of the philosophical faculty of the University of Zurich have approved the study protocol, informational letter, and informed consent process.

### Eligibility criteria

Patients will be eligible for the study if they meet the following criteria: (1) current diagnosis of opioid dependence (ICD-11), (2) receiving methadone or buprenorphine maintenance treatment for at least two weeks and not more than eight weeks, (3) ownership of a smartphone, (4) access to the Internet, (5) minimal age of 18 years, (6) provide written informed consent, (7) good command of and ability to read and write Persian. Exclusion criteria are (1) concurrent diagnosis of any other substance dependence (except tobacco) and (2) current severe or acute psychiatric disorders.

### Recruitment

The study will be advertised at drug treatment centers and other treatment settings where patients with opioid dependence are prevalent. Patients will be recruited at the INCAS clinic (https://enincas.tums.ac.ir), and seven further selected clinics in Tehran from patients recently admitted to OMT programs, including methadone and buprenorphine maintenance treatments. Patients interested in study participation will be informed about the study’s rationale, as well as: [1] study inclusion and exclusion criteria; [2] the two different study arms and their chance of being allocated into each one; [3] potential risks of participation; [4] safety arrangements during and after the study phase; [5] inability of the PROMPT intervention to replace face-to-face OMT; and [6] circumstances under which they should contact a professional at their treatment center. Moreover, they will be informed about their voluntary participation and their right to withdraw from the study at any time without consequences, except for the loss of further compensation. Written informed consent must be provided for study participation.

### Randomization

After potential participants have provided informed consent, been deemed eligible according to inclusion and exclusion criteria, and have completed the baseline assessment, participants will be randomized by an automated computer program into either the treatment or control group in a 1:1 ratio. Completion of each follow-up assessment will result in participants being compensated with an equivalent of 5 CHF via an online voucher. Figure 1 provides an overview of the trial flow.

**Fig. 1 Fig1:**
[figure not shown]
Flow diagram

### Sample size

Based on the results of a systematic review and meta-analysis on internet interventions in adults with opioid dependence [17], we expect a Cohen`s d of about 0.35, comparing Study arm 1 (PROMPT) and Study arm 2 (OMT as usual). An overall sample size of N = 400 participants would have 80% power to detect the expected effect size when modeling a three-level generalized linear mixed model with six measurements (baseline, 1-, 2-, 3-, 6-, and 12-month follow-up) and eight treatment centers. Respective indices of baseline variance at the participant and treatment center level, as well as slope variance at the center level, and moderate heterogeneity in change over time, were based on a psychotherapeutic simulation study [18]. This calculation also considers an expected dropout rate of 30%, with a higher risk of dropout towards the end of the study. Calculations were performed using the package powerlmm in R [19].

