### Opioid maintenance therapy as usual

Certified opioid agonist treatment centers provide OMT services through a multidisciplinary team consisting of a trained general physician, clinical psychologist, and nurse. Physician visits, counseling sessions, and the dispensing of opioid agonist medications are all provided at the centers. Each multidisciplinary team is allowed to provide treatment for a maximum of 230 OMT patients, including 100 patients on methadone, 80 receiving buprenorphine, and 50 receiving opium tincture.

The type of treatment regime (i.e., assisted withdrawal, maintenance treatment) and agonist medication (methadone or buprenorphine) are chosen by the professionals based on patients’ substance use history and previous experiences with opioid pharmacotherapies and preferences. General guidelines exist for opioid agonist induction, which the physician tailors to patients’ needs. There is no upper or lower dose limit for methadone during the maintenance phase, although methadone doses ranging from 80 to 120 mg/day are generally considered optimal. Due to buprenorphine’s “ceiling effect” in doses above 32 mg/day, physicians may prescribe up to 32 mg of buprenorphine daily. However, it has been demonstrated that daily doses exceeding 24 mg yield minimal clinical benefits. Consequently, physicians are advised to reevaluate the patient’s condition and contemplate alternative therapeutic approaches if stabilization cannot be attained at this dosage level.

During treatment, patients are regularly visited by a general physician and participate in weekly individual counseling sessions with the center’s clinical psychologists for the first 12 weeks of treatment. Morphine and methamphetamine urine tests are obtained routinely to monitor concurrent illicit substance use. At the beginning of OMT, patients must regularly come to the center and consume their dose under professional supervision. Contingent to the behavioral stabilization (i.e., regular attendance and negative urine tests), take-home doses start and may increase gradually to up to two weeks from the start of their fourth month of treatment [12, 20].

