Furthermore, any negative effects due to the smartphone intervention will be measured via the Negative Effects Questionnaire [30] at all follow-up assessments. As an indicator of treatment adherence, data will be collected on how many modules have been completed and how many OMT physicians’ visits and counseling sessions are attended by each participant. The primary and secondary outcomes and the exact time points at which each measure will be applied are presented in Table 2.

**Table 2 Tab2:** Overview of measures and their time of assessment

	Baseline	Month 1	Month 2	Month 3	Month 6	Month 12
Sociodemographic characteristics	x					
Addiction treatment history	x					
Percentage of negative urine tests (illicit, non-prescribed opioids)		xxxx	xxxx	xxxx	x	x
The longest period of abstinence from the illicit opioids		x	x	x	x	x
Number of missed OMT appointments		x	x	x	x	x
Blood-borne Virus Transmission Risk Assessment Questionnaire (BBV-TRAQ)	x			x	x	x
Number of self-reported opioid use/free days - (TLFB)	x	x	x	x	x	x
Self-reported other street-drug use/free days - (TLFB)	x	x	x	x	x	x
Perceived Stress Scale (PSS-10)	x			x	x	x
Patient Health Questionnaire for Depression (PHQ-9)	x			x	x	x
Generalized Anxiety Disorder Screener (GAD-7)	x			x	x	x
International Trauma Questionnaire for PTSD (ITQ)	x			x	x	x
Client Satisfaction Questionnaire (CSQ-8)		x	x	x	x	x
Negative Effects Questionnaire		x	x	x	x	x
Methamphetamine (MA) urine test (monthly)	x	x	x	x	x	x
Benzodiazepine urine test (monthly)	x	x	x	x	x	x
THC urine test (monthly)	x	x	x	x	x	x
HIV test result	x			x	x	x
Adult ADHD Interview (NSC-R)	x					
Alcohol Use Disorder Identification Test (AUDIT)	x			x	x	x
Fagerstrom Test for Nicotine Dependence (FTND)	x			x	x	x

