### Statistical analyses

Data will be analyzed according to the intention-to-treat principle (ITT). We will examine for differences in all primary and secondary outcome variables between the two study arms at baseline and follow-up assessments using (generalized) linear mixed models. We will specifically model repeated measures nested within participants and participants nested within treatment centers by defining respective random intercepts and slopes. Study conditions and time will be modeled as fixed effects. Appropriate distributions for non-normal continuous and/or count outcomes will be specified (e.g., negative binomial, zero-inflated, Poisson). Subject to the sample’s actual gender distribution, we will investigate the intervention’s gender-specific effects by including a gender*treatment*time interaction term. If this is not possible due to inadequate sample size (i.e., the model is not identifiable), separate subgroup analyses will be run, which will allow the determination of differential treatment effects.

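### The 80% power is stated for six measurements including baseline, but the primary opioid urine outcome has only five values, all after baseline

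*Protocol article*

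**What the plan says.** **Sample size.** The article expects a Cohen's "d of about 0.35, comparing Study arm 1 (PROMPT) and Study arm 2 (OMT as usual"). It continues: "An overall sample size of N = 400 participants would have 80% power to detect the expected effect size", under a "three-level generalized linear mixed model with six measurements (baseline, 1-, 2-, 3-, 6-, and 12-month follow-up") in eight centres. It names as inputs baseline variances at participant and centre level, a slope variance at centre level and moderate heterogeneity of change, all taken from a cited simulation study and given without values. Dropout of 30%, heavier towards the end, is allowed for. The section does not say which of the two primary outcomes the figure refers to.

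**Primary and secondary outcomes.** The urine outcome is the share of negative opioid tests in the interval from one assessment to the next. In Table 2 the row "Percentage of negative urine tests (illicit, non-prescribed opioids") has an empty baseline cell, four marks in each of months 1, 2 and 3, and one mark each at months 6 and 12. In the same table "Methamphetamine (MA) urine test (monthly"), the benzodiazepine and THC urine tests, and self-reported opioid-free days (TLFB) are all marked at baseline.

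**Statistical analyses.** Arm differences on every primary and secondary outcome are to be examined at baseline as well as at follow-up, with random intercepts and slopes. "Study conditions and time will be modeled as fixed effects".

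**Opioid maintenance therapy as usual.** "Morphine and methamphetamine urine tests are obtained routinely".

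**The concern.** Two sections count a baseline value that a third does not schedule. This is a contradiction inside the article, not a detail that a separate analysis plan would supply. The blank does not look like a slip in the table: other urine tests are marked at baseline, and six time points bound only five intervals.

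Three things are at stake:

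- **The power claim.** The inputs that the article names (baseline variance, slope variance, heterogeneity of change) suggest that the powered effect is change from baseline. If so, the calculation used information that this outcome will not provide.
- **The meaning of a slope.** With no baseline value, an arm-by-time slope asks only whether the arms diverge after month 1. The smartphone intervention is expected to run for three months, so an early benefit that is then maintained is plausible. A slope starting at month 1 would miss it.
- **Precision and balance.** Participants enter after two to eight weeks of maintenance treatment, so opioid use at entry may vary. Without a baseline value, balance on this outcome cannot be seen directly, and precision from baseline opioid use is lost unless another measure is used as a covariate.

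**Working it through.** **1. Count the values.** Sample size: 6 (months 0, 1, 2, 3, 6, 12). Table 2 and the interval definition: 5 (months 1, 2, 3, 6, 12). Reading the power as referring to retention does not remove the mismatch, because retention is defined as a weekly percentage and is not a six-point outcome with a baseline variance.

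**2. Try to reproduce the 80%.** This cannot be done by the article's own method, because alpha, variance inputs and dropout curve are missing. A rough check with a two-sided 5% test of two means (normal approximation): n per arm = 2(1.960 + 0.842)² / 0.35² = 128.1, so 129; total 258; 258 / 0.7 = 368.6, so 369 with 30% dropout. With N = 400 and 140 completers per arm, power is about 83%. N = 400 is thus the right order of magnitude, but this is not the stated calculation.

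**3. Information about a linear slope.** Sxx = Σt² − (Σt)²/n.
- Six points: 194 − 24²/6 = 98.0
- Five points: 194 − 24²/5 = 78.8

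**4. Power with and without baseline.** Assumptions: linear mixed model with patient random intercept and slope, total variance at baseline set to 1, N = 400 (1:1), two-sided 5%, retention 1 − 0.3(t/12)², and a linear effect reaching 0.35 at month 12. The effect per month is 0.35/12 = 0.02917. Power = Φ(effect/SE − 1.96). The variances (intercept, slope, residual) are assumed and chosen so that six points give about 81%.

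| Variances | Slope test, 6 → 5 points | Rise in slope SE | Month-12 difference, 6 → 5 points |
|---|---|---|---|
| 0.3, 0.001, 0.7 | 80.7% → 72.3% | 11% | 87.2% → 85.7% |
| 0.4, 0.002, 0.6 | 81.0% → 73.4% | 10% | 83.1% → 81.7% |
| 0.5, 0.003, 0.5 | 81.4% → 74.8% | 8.5% | 79.2% → 78.0% |

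First row in full: the SE rises from 0.01031 to 0.01143; 0.02917/0.01031 − 1.96 = 0.87, giving 81%; 0.02917/0.01143 − 1.96 = 0.59, giving 72%. A constant difference of 0.35 tested as a level over the five follow-ups has about 99% power in all three settings.

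**5. Wider range.** A three-level version used eight centres, 25 patients per arm per centre, participant intercept share 0.3–0.7, centre share 0.02, centre share of slope variance 0 or 0.05, and three dropout shapes. Slope variance was solved so that six points give exactly 80%. With five points the slope test has about 72–76%, the month-12 difference about 69–86%, and a constant difference more than 97%.

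**6. Early, maintained benefit.** If the arm difference is 0.35 at each of months 1, 2, 3, 6 and 12, its slope over those months is zero. A five-point slope test then rejects only at its type I error rate, whereas a level contrast detects the benefit.

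**7. Value of a baseline covariate.** With an assumed correlation r = 0.3–0.5 between baseline and follow-up, residual variance falls by r² = 9–25%. That equals 1/(1 − r²) − 1 = 10–33% more patients.

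**The case against.** The strongest reply is that the size of the loss depends on a test that the article never names. It specifies condition and time as fixed effects and arm differences at assessments. It does not say that time is linear or that the arm-by-time slope is the only test, and such detail may sit in an analysis plan that is not shown. For a month-12 difference, losing baseline costs 1–2 points in the settings above; for a constant difference, power is ample. This stands, and it limits the claim about size. It does not remove the contradiction over how many values exist.

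A reader might infer three stronger things that the documents do not support:

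- *That the 80% is wrong.* With the inputs not given, it can be neither confirmed nor refuted.
- *That the trial has 5% power against an early benefit.* This holds only for a slope-only test starting at month 1, which the article does not state.
- *That imbalance in baseline opioid use cannot be corrected.* Baseline TLFB opioid-free days are collected and can serve as a covariate, and randomisation keeps the unadjusted comparison valid. An article that names no covariates is not in error for that.

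It is also fair to say that one baseline strip gives a positive or negative result, not the interval percentage. It could be a covariate but not a sixth outcome value.

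**Conclusion.** The inconsistency holds: the stated power is for a measurement schedule that the primary urine outcome does not have, and the promised baseline comparison on this outcome cannot be made as scheduled. The consequence is moderate and depends on the contrast: from about 80% to 72–76% for a slope test, little change for a month-12 difference in the three settings shown, and more than 97% for a constant difference. These figures rest on assumed variances, alpha and dropout, on a linear approximation to the generalised model, and on equal residual variance at all visits, although Table 2 shows four tests a month early on and single marks at months 6 and 12.

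The validity of the randomised comparison is not threatened. What is lost is precision and a direct view of baseline balance on this outcome. The point deserves correction but is not critical.

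**What to change.** 1. Reconcile Sample size, the outcome definition, Table 2 and Statistical analyses on the number and timing of the urine values.
2. Recompute and restate the power for the five values actually taken. Say which primary outcome and contrast it refers to, and give alpha, variance inputs and dropout curve.
3. Make the primary contrast the arm difference at, or averaged over, post-baseline visits, with time as categories, rather than a slope starting at month 1.
4. Adjust the urine model for baseline TLFB opioid-free days. If the opioid panel is also run on the baseline urine sample, add the result as a binary covariate, not as a sixth outcome value. The latest routine morphine test before randomisation is a fallback, but it may not cover tramadol.

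**Cost.** One test strip on an existing sample (none if only TLFB is used), one or two covariates, and a rerun of the power script. The restated power may be less favourable. A baseline sample not tested for opioids may not be recoverable after randomisation; for patients already enrolled, TLFB may be the only option.

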### Opioid maintenance therapy as usual

Certified opioid agonist treatment centers provide OMT services through a multidisciplinary team consisting of a trained general physician, clinical psychologist, and nurse. Physician visits, counseling sessions, and the dispensing of opioid agonist medications are all provided at the centers. Each multidisciplinary team is allowed to provide treatment for a maximum of 230 OMT patients, including 100 patients on methadone, 80 receiving buprenorphine, and 50 receiving opium tincture.

The type of treatment regime (i.e., assisted withdrawal, maintenance treatment) and agonist medication (methadone or buprenorphine) are chosen by the professionals based on patients’ substance use history and previous experiences with opioid pharmacotherapies and preferences. General guidelines exist for opioid agonist induction, which the physician tailors to patients’ needs. There is no upper or lower dose limit for methadone during the maintenance phase, although methadone doses ranging from 80 to 120 mg/day are generally considered optimal. Due to buprenorphine’s “ceiling effect” in doses above 32 mg/day, physicians may prescribe up to 32 mg of buprenorphine daily. However, it has been demonstrated that daily doses exceeding 24 mg yield minimal clinical benefits. Consequently, physicians are advised to reevaluate the patient’s condition and contemplate alternative therapeutic approaches if stabilization cannot be attained at this dosage level.

During treatment, patients are regularly visited by a general physician and participate in weekly individual counseling sessions with the center’s clinical psychologists for the first 12 weeks of treatment. Morphine and methamphetamine urine tests are obtained routinely to monitor concurrent illicit substance use. At the beginning of OMT, patients must regularly come to the center and consume their dose under professional supervision. Contingent to the behavioral stabilization (i.e., regular attendance and negative urine tests), take-home doses start and may increase gradually to up to two weeks from the start of their fourth month of treatment [12, 20].

